### Assessments

At baseline, participants will complete computerized surveys prior to being randomized. They will then go immediately to their first intervention session, either to receive their brochures or to attend their first educational unit. To assess knowledge acquisition, intervention participants will have their 1st follow-up assessment 1 week after the last intervention session with control participants matched to the same interval. Subsequent follow-up assessments will occur at 6, 12, 18, and 24 months from the date of randomization. We will measure outcomes using in-person computerized surveys at baseline and 1 week after the last intervention session. All other follow-ups will use secure web-based surveys linked only by participant codes to protect privacy.

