### Outcome measures

#### Primary

Completed sexual assault (rape) will have occurred when a participant indicates she has had at least one experience of sexual intercourse (oral, anal, or vaginal) that was threatened, forced, or drugged (completed, not attempted) in the period between the previous outcome measurement and the present; answered ‘once’ or more to any of 9 questions (involving oral sex, vaginal penetration, and/or anal penetration “without consent” when the woman was “too drunk or out of it to stop what was happening”, was threatened with physical harm to herself or others she cares about, and/or was forced, “for example holding me down with their body weight, pinning my arms, or having a weapon”) on the *Sexual Experiences Survey* - *Short Form Victimization* SES-SFV, [71]. Month of occurrence will be recorded to permit time-to-event analyses. Previous versions of the SES have been used in large university, college, and community samples, and it is considered the gold standard. Responses on the scale are stable across administrations. Test-retest reliability is very high, and responses are also comparable to those received through interviewing women [72]. Concurrent validity has been demonstrated using correlations between sexual victimization as measured with the SES and variables predicted to be affected or influenced by that victimization, for example, hostility toward men [73,74]. Construct validity has been demonstrated when women’s descriptions of sexual experiences were rated by interviewers (on the items of the SES) and compared to the women’s own responses on the SES [75].

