### Sample size considerations

The primary outcome is completed sexual assault (rape). Our 2006–2007 pilot randomized controlled trial of 214 students yielded the following cumulative incidences. For women in the control arm, the 3- and 6-month rates were 12% and 20%, respectively. For those in the sexual assault resistance education program, they were 6% and 11%, respectively. These figures correspond to a 50% relative risk reduction. This is comparable to the one previous study conducted by Hanson and Gidycz [49], which yielded a rate of 14% of rapes in their control arm and 6% in their intervention arm over a 3-month period, among women with no history of previous victimization. Given that the incremental incidence of sexual assault declines over time we estimate, for the purpose of sample size calculations, the 1-year rates to be 25% in the brochure arm and 17.5% in the educational program arm; a more conservative 30% relative risk reduction. Therefore, a sample size of 932 women (466 per group) will have 80% power to detect an absolute difference of 7.5% (25% versus 17.5% equals a 30% relative reduction) at a two-sided 5% level of significance. This is a meaningful reduction because it implies that for every 14 women who enroll in the program, 1 additional rape could be averted. Aside from power considerations, it is important to note that a sample of this size will yield a significantly positive trial when the observed difference between groups is as small as 5.4% (21.6% relative risk reduction). Although the intracluster correlation was calculated as −0.02 from our pilot study, +0.02 will be used to inflate the sample size with a design effect of 1.38 and a cluster size of 20 women. Assuming a lost-to-follow-up of 10% in the first year and 15% in the second year of follow-up, the total size of the trial will be 1716 women (932×1.38÷0.75).

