### Statistical analyses

Analyses will be performed after all women have completed their one-year follow-up and at the end of the trial. Following the intention-to-treat principle, a participant will be included in the analysis if she is randomized. Using SAS software [92] the primary (and tertiary) analyses will compare the proportion of women with completed sexual assaults between groups using a Wald test from a log-binomial regression model (PROC GENMOD) that adjusts for compound symmetry (CS) clustering using generalized estimating equations. Covariates will be added to the model if differences among baseline characteristics are observed. In addition, a test for interaction will be performed using the above model to assess whether there is a differential treatment effect depending upon whether the women participated in the weekend versus weekday programs. Women who are lost to follow-up or drop out can affect the validity of the group comparison if (a) sexual assault is related to being lost or dropped and (b) it is differential between groups. Thus, baseline characteristics of women who are lost and drop out will be compared to women who complete the trial. In addition, the missing data mechanism will be formally tested [93] to determine whether it is Missing Completely at Random (MCAR) or is Missing at Random (MAR). Freedom from completed sexual assault will be compared between groups using Cox regression (PROC PHREG) with a robust sandwich covariance matrix to account for the clustering. Women who are lost to follow-up or drop out will have their data censored at the time of last contact.

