For the secondary outcomes which are all continuous (or at least ordinal) longitudinal, repeated measures analysis of covariance (ANCOVA) will be used to compare intervention arms across the follow-up periods, adjusting for baseline scores on the instruments. Generalized linear models (PROC MIXED) will be used to correctly adjust the variance estimates for CS clustering. Recognizing that some of the instruments have ordinal responses, a rank-based ANCOVA will also be performed to assess congruency with the parametric analyses. For completeness in assessing the effect of missingness, two additional analyses will be conducted: (a) a ‘per-protocol’ analysis among participants who attend all sessions and respond to the 1-year SES-SFV questions; (b) multiple imputation of five data sets (PROC MI and MIANALYZE) using a discriminant function for binary outcomes and Markov chain Monte Carlo for continuous outcomes, assuming the missing data mechanism is MAR. The literature, for example [49], suggests that prior sexual assault can be a modifier with respect to the effectiveness of sexual assault resistance programs. Accordingly, program effects will be compared for women with and without sexual assault histories at baseline.

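### Five imputations and a normal-theory discriminant function are weak choices for the supplementary missing-data analysis: near the 5% level its p-value can depend on the seed, and both are cheap to replace

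*Protocol article*

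**What the plan says.** In the Protocol article, Statistical analyses, the main comparison of the proportions assaulted is a Wald test from a log-binomial model with generalized estimating equations. The section then adds: "For completeness in assessing the effect of missingness, two additional analyses will be conducted". One is a per-protocol analysis. The other is "multiple imputation of five data sets (PROC MI and MIANALYZE) using a discriminant function for binary outcomes", with Markov chain Monte Carlo for continuous outcomes, "assuming the missing data mechanism is MAR". The same section describes the secondary outcomes as continuous or at least ordinal, so the binary outcomes meant here must be the assault outcomes.

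Three other statements bear on the point:
- Sample size considerations sets the amount of missing data: "Assuming a lost-to-follow-up of 10% in the first year and 15% in the second year of follow-up".
- The primary outcome is recorded by interval, "in the period between the previous outcome measurement and the present".
- On timing, Assessments says: "Subsequent follow-up assessments will occur at 6, 12, 18, and 24 months from the date of randomization".

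The article does not say which assault variable is imputed (interval or cumulative) or which predictors enter the imputation model.

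**The concern.** The number of imputations and the imputation method are stated choices, not details left open, so they can be judged as they stand.

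First, the pooled estimate from five imputations still carries visible random error from the imputation itself. Two analysts with the same data and different seeds can get different p-values, and near 0.05 they can reach opposite readings.

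Second, a discriminant function treats the predictors as normal with a common variance among assaulted and non-assaulted women. The obvious predictor of one-year status is the six-month report, which is yes/no. If the outcome is cumulative, every six-month 'yes' is also a one-year 'yes'. The assaulted group is then a mixture of 0s and 1s, and the other group is all 0s. Neither normality nor equal variance is close to true.

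At stake is how well a sensitivity analysis can show whether loss matters. The article itself says loss can invalidate the comparison if it is related to assault and differs between groups, and under Differential drop out it expects that control participants may be likelier to leave. The companion per-protocol analysis keeps only women who attended every session and answered at one year, so it recovers no lost women.

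**Working it through.** **The plan's own figure.** For 25% v 17.5%, two-sided 5%, 80% power, pooled variance: n = [1.96·√(2·0.2125·0.7875) + 0.842·√(0.25·0.75 + 0.175·0.825)]² / 0.075² ≈ 466 per group, as stated. The design effect is 1 + 19·0.02 = 1.38, and 932·1.38/0.75 = 1714.9, against the stated 1716. The plan gives no figure for the precision of the imputation analysis.

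**Inputs.** 1716/2 = 858 women per arm. A 10% loss leaves 772 per arm and a 25% loss leaves 644. Variances are multiplied by 1.38.

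**A borderline data set (chosen for illustration).** 193/772 v 154/772, risk ratio 0.80.
- Log risk ratio = ln(154/193) = −0.226.
- Variance = 1.38·[0.750/193 + 0.801/154] = 0.01254; SE = 0.112.
- z = 2.016, complete-case p = 0.044.

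**Seed dependence by simulation.** Missing status was drawn by arm from the posterior of the observed rate, pooled by Rubin's rules on the log risk ratio, with 2,000 seeds.

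| Missing | Events | Complete-case p | Imputations | Central 95% of p | Above 0.05 |
|---|---|---|---|---|---|
| 10% | 193 v 154 | 0.044 | 5 | 0.022 to 0.078 | 30% |
| 10% | 193 v 154 | 0.044 | 100 | 0.036 to 0.047 | 0.1% |
| 10% | 193 v 150 | 0.026 | 5 | – | 2% |
| 10% | 193 v 145 | 0.012 | 5 | – | 0% |
| 10% | 193 v 135 (planned effect) | 0.002 | 5 | – | 0% |
| 25% | 161 v 126 | 0.047 | 5 | 0.012 to 0.13 | 42% |
| 25% | 161 v 126 | 0.047 | 100 | 0.031 to 0.051 | 3% |

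**Hand check (first data set).** The between-imputation variance is about [f + f²·(858/772)]·S, where f = 0.10 and S = (0.750/193 + 0.801/154)·772/858 = 0.0082. This gives B ≈ 0.111·0.0082 = 0.00091. The Monte Carlo SD of the pooled log risk ratio is √(B/m), and the pooled SE is about 0.111.
- m = 5: 0.0135, or 0.12 in z. z = 2.03 ± 1.96·0.12 gives p from about 0.023 to 0.073.
- m = 50: 0.0043, or 0.039 in z. z = 2.04 ± 0.076 gives p from about 0.034 to 0.049.
- m = 100: 0.0030, or 0.027 in z. z = 2.04 ± 0.053 gives p from about 0.036 to 0.047.

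This agrees with the simulation.

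**A separate simulation** used the discriminant function with arm as the only predictor, on data sets further from the threshold (median p about 0.025 and 0.03). At five imputations 4% of seeds crossed 0.05 with 10% missing and 29% with 25% missing. None crossed at 50. It used 100 seeds at five imputations and 25 at 50, so these shares are illustrative.

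**Discriminant function with the six-month report as predictor.** The pilot figures are: "For women in the control arm, the 3- and 6-month rates were 12% and 20%, respectively"; the six-month program figure is 11%. The planned one-year rates are 25% and 17.5%.
- Control: the mean of the report is 0.20/0.25 = 0.8 among the assaulted and 0 otherwise. Pooled variance = 0.25·0.8·0.2 = 0.04. Logit after a 'no' = ln(0.25/0.75) − 0.8²/(2·0.04) = −1.10 − 8.00 = −9.10, a risk of 0.01%. Implied risk = (25 − 20)/80 = 6.3%.
- Program: mean 0.11/0.175 = 0.629; pooled variance 0.175·0.629·0.371 = 0.0409. Logit = −1.55 − 4.84 = −6.39, a risk of 0.17%. Implied risk = (17.5 − 11)/89 = 7.3%.

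The separate simulation, with one model for both arms, gave about 0.06% against 6.4% and 7.2%. At 25% missing this lowered the imputed-data rates by 1.3 and 1.7 percentage points.

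**The case against.** Much of the case for leaving the plan alone is sound.

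- **The analysis is supplementary.** The primary p-value does not use it. The article also compares the baseline characteristics of lost women, tests the missingness mechanism, runs a Cox model that censors at last contact, and offers women who stop a telephone survey at one and two years. This stands and limits the weight of the point.
- **Five imputations are valid.** Rubin's rules allow for a finite number, and relative efficiency is 1/(1 + 0.10/5) = 98% for 10% missing information and 95% for 25%. This is correct. The issue is reproducibility of a near-threshold p-value, not bias or type I error.
- **The 25% figures apply at 24 months only.** The one-year primary comparison has 10% planned loss. This stands.
- **The implied 6% to 7% mixes sources.** It sets pilot six-month rates against more cautious planning rates for one year, which is why the program arm's second-half risk comes out above control's. Those values are rough, but the contrast with 0.01% and 0.2% does not depend on their exact size.

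Three stronger readings are tempting, and the documents do not support them.

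- A reader might infer that imputed values will contradict six-month reports already in hand. That happens only if a cumulative outcome is imputed without the six-month report. With the report as predictor, the simulation found no six-month 'yes' imputed as 'no', and imputing by interval rules it out. The article does not state which model is used, and it collects the outcome by interval.
- A reader might infer that the imputed risks are wrong whichever model is used. Interval imputation is a third option that the article leaves open.
- A reader might infer a material bias in the risk ratio. On the plan's rates, with 10% lost at random after six months, the discriminant step gives 25 − 0.1·0.8·6.24 = 24.5% and 17.5 − 0.1·0.89·7.13 = 16.9%, a ratio of 0.69 instead of 0.70. A larger shift needs an assumed unequal loss and an omitted six-month report, and a logistic model omitting that report would shift in the same way.

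**Conclusion.** The point holds as a minor, cheap improvement. Five imputations are too few for a stable p-value when the result is close to 5%: about 30% of seeds cross 0.05 at complete-case p = 0.044 with 10% missing, about 2% at p = 0.026, and none at the planned effect. One hundred imputations nearly remove the noise. The discriminant function is a poor model if a cumulative outcome is predicted from the six-month report, because it almost erases new events after a six-month 'no'.

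The first conclusion assumes loss at random within arm, clustering handled through the 1.38 design effect, and a result near the threshold. The second depends on a cumulative outcome with the six-month report as predictor, which the article neither states nor excludes. The primary test is unaffected.

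**What to change.** In Statistical analyses, change the number of imputed data sets from five to at least 50, preferably 100. At 25% loss, even 100 left about 3% of seeds above 0.05 in a borderline case. Replace the discriminant function with logistic imputation in the same procedure (PROC MI, FCS LOGISTIC), run separately by arm.

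Preferably, impute assault in each survey interval (0–6, 6–12, 12–18 and 18–24 months) given earlier reports, assault history and site, and then derive the cumulative yes/no. Reports already given are then kept as they are. It also avoids fitting a logistic model in which a six-month 'yes' predicts the cumulative outcome perfectly.

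The cost is a one-sentence edit, minutes of computing and slightly more programming for the interval-wise version. No new data are needed. The article describes the trial as still enrolling, so the change can be fixed before the one-year analysis.

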### Ethical considerations

Ethical approval for the trial was received from the University of Windsor Research Ethics Board on May 31, 2011, from the University of Guelph’s Research Ethics Board on June 14, 2011 and from the University of Calgary’s Conjoint Health Research Ethics Board on September 9, 2011. There are no serious anticipated risks to participants, although the content of the educational interventions and some survey questions on sexual assault could bring up negative feelings for participants, particularly if they have an assault history. The self-defence instruction adds limited physical risk if participants do not follow instructions carefully. In our pilot studies involving over 200 women, none reported adverse effects.

### Steering committee and trial oversight

The Steering Committee for the trial will consist of the Principal Investigator and four Co-Investigators. A Data Safety Monitoring Committee is not needed as our psychosocial intervention does not warrant it. The Trial Project Manager will make decisions for all sites on trial issues that arise and communicate with the Site Coordinators to ensure consistency on these issues. The Trial Project Manager will be supervised by the Principal Investigator and the Site Coordinators will be supervised by the Site Investigators. Research Assistants will be supervised by Site Coordinators. The Trial Project Manager, Principal Investigator, and Co-Investigators will meet monthly by teleconference and annually in person.

Intervention conformity will be measured by having site facilitators complete a Session Protocol Issues form at the end of each unit and by review of audio recordings of randomly selected sessions for each facilitator. Audio recordings will be reviewed by the Trial Project Manager and any outstanding issues will be addressed in special meetings. Protocol issues identified by facilitators will be addressed in weekly meetings.

### Trial status

The first participant was randomized on September 28, 2011. Currently, 918 women have been enrolled into the on-going trial.

## Discussion

On university campuses, sexual assault rates are high, especially among first- year female students. Therefore, these young women represent a critical population for resistance education interventions. There is now a consensus that relying solely on coeducational or men’s programs is insufficient to fully protect women from sexual assault. Programming that empowers women with knowledge, skills, and practice to resist coercive sexual behaviours from known men is needed. The proposed randomized controlled trial is an evaluation of a sexual assault resistance education program, designed to reduce sexual assault among young women in the first year of university. We believe that reductions in sexual assault will have a direct impact on the mental and physical health of all women at university, but particularly for those who are able to successfully resist completed sexual assault.

The results of the trial will provide a unique contribution to the published literature, in addition to producing a maximally effective sexual assault resistance education program and an accompanying facilitator training manual which can be adopted by universities. The trial results will also provide direction for further research into which aspects of the program need to be strengthened, as well as how long the effects of the program last and will indicate at which point in time refresher sessions may be necessary. If the program is effective, this may also provide an entry to implementation and research in high school and to other populations of young women who are not enrolled in university.
